### Outcome Measures

The following demographic information will be collected before the start of the trial: age, sex, educational attainment, marital status, number of children, length of time since diagnosis, disease course, relapse history, employment status, prescribed drugs currently taken, co-morbid medical conditions, disability level.

For those randomised to the FMP, outcomes will be measured 1 week prior to the start of the programme and 1 month, 4 months and 12 months after the end of the programme. For those randomised to current local practice, outcomes will be sent on the same dates as those randomised to the FMP.

### Primary Outcome Measures

These are all self-reported questionnaire measures and specified *a priori*.

There are three primary outcomes:

#### 1. Self-reported fatigue severity

The Fatigue Assessment Instrument (FAI) [55] is an expanded version of the uni-dimensional Fatigue Severity Scale (FSS) [51]. The FSS is one of the best known and most used fatigue scales. It principally measures the impact of fatigue on specific types of functioning. The FAI has four subscales: fatigue severity, situation specificity, consequences of fatigue, and responsiveness to rest/sleep. Responses are made on a 7-point Likert-type scale. The fatigue severity subscale of the FAI corresponds almost exactly to the Fatigue Severity Scale, sharing eight of the original nine items along with three additional items. Scores on this subscale are a primary outcome. The other subscales are secondary outcomes.

#### 2. Self-reported MS-specific quality of life

The Multiple Sclerosis Impact Scale (MSIS-29) [56,57] measures the physical (20 items) and psychological impact (9 items) of MS on day-to-day life. It uses 5-point Likert-type scales ranging from 'not at all' to 'extremely' and is based on quality of life in the last two weeks. The total score for the MSIS-29 is a primary outcome measure. The physical and psychological subscales will be secondary outcomes.

#### 3. Self-reported self-efficacy for managing fatigue

The Multiple Sclerosis-Fatigue Self-Efficacy (MS-FSE) scale is adapted from the Control subscale of the MS Self-Efficacy (MSSE) Scale developed by Schwartz [58]. This adapted scale has undergone a preliminary validation in our pilot research.

### Secondary Outcome Measures

#### Self-reported fatigue

Three of the subscales from the FAI [55] (namely, situation specificity, consequences of fatigue and responsiveness to rest/sleep) along with the total score of the FAI.

#### Self-reported MS-specific quality of life

The subscale scores of the MSIS-29 [56,57] for the physical and psychological impact of MS.

#### Self-reported general quality of life

1. The Medical Outcomes Short-Form Survey version 2 (SF-36v2) [59,60] measures eight dimensions: physical functioning, role limitations because of physical health problems, bodily pain, general health perceptions, vitality, social functioning, role limitations because of emotional problems, and mental health. It generates scores for the eight dimensions as well as two summary measures (physical health and mental health). It uses Likert-type response scales. This measure will also be used to calculate Quality Adjusted Life Years (QALYs) for the economic analysis.

2. The EuroQoL (EQ-5D) [61] is a standardised instrument for use as a measure of health outcome. It has been developed by the EuroQoL Group as a simple, generic measure of health status, and is applicable to a wide range of health conditions. The EQ-5D consists of the EQ-5D descriptive system and the EQ visual analogue scale (EQ VAS) and it allows the derivation of a single index value for health status. The EQ-5D descriptive system comprises five dimensions (mobility, self-care, usual activities, pain/discomfort and anxiety/depression) each rated on three levels (no problems, some problems, severe problems). The EQ VAS records the respondent's self-rated health on a vertical, visual analogue scale where the endpoints are labelled 'best imaginable health state' and 'worst imaginable health state'.

#### Self-reported mood

The Hospital Anxiety and Depression Scale (HADS) [62] is a self-report measure consisting of an anxiety and a depression subscale. Each subscale consists of 7 items with a 4-point Likert-type response scale.

#### Self-reported fatigue severity

The Fatigue Symptom Inventory (FSI) [63,64] is a 14-item self-administered multi-dimensional questionnaire which measures the severity, frequency, and diurnal variation of fatigue and its perceived interference on quality of life. Severity is measured using four separate items that assess most, least, and average fatigue in the past week, as well as current fatigue. Frequency is measured using two separate items that assess the number of days in the past week that respondents felt fatigued, as well as the portion of the day on average they felt fatigued. Diurnal variation is measured using a single item that provides descriptive information about daily patterns of fatigue. Perceived interference is measured using seven separate items.

#### Self-reported sleep quality

These questions have been modified from the MS Clinical Practice Guidelines sleep questionnaire [7]. Questions include duration and quality of night-time sleep, factors that may prevent or interrupt sleep, and daytime sleeping and sleepiness.

#### Self-reported resource utilisation

A resource utilisation questionnaire will be administered at 4- and 12-month follow-up. It is adapted from one utilised in a large randomised controlled trial in Parkinson's disease [65], and includes questions about health and social service contacts in the preceding 3 months.

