### Intervention

The group-based fatigue management intervention [45] is based upon a conceptual framework that integrates elements from cognitive behavioural [70], social-cognitive [71], energy effectiveness, self-management [72] and self-efficacy [73] theories.

The intervention focuses on the management of fatigue, the most common symptom of MS, and is likely to be relevant to many people. However, it is expected that it will also provide a framework to help people manage their MS more generally. A cognitive behavioural approach that focuses on one symptom is likely to be clearer and less overwhelming than one encompassing many aspects, can be achieved in a smaller number of sessions, and will be easier to integrate within existing services.

The intervention consists of six sessions held on a weekly basis; the first, 2 hours' duration, and subsequent sessions, 1.75 hours' duration (each with a 15 minute refreshment break halfway through). It is designed to be run by two health professionals with experience of working with people with MS and of group-work (such as occupational therapists, nurses, or physiotherapists). This latter feature enables the intervention to be incorporated into existing health service structures. The intervention will be delivered to groups of 6-12 people.

Participants are encouraged to bring along a "supportive other" to the first session. Since the intervention entails participants making lifestyle changes, the involvement of a "supportive other" could help to encourage and support them in making such changes. Contact between members of the group outside the formal group setting will be encouraged, as an additional source of support.

The intervention is manualised and sessions are delivered via PowerPoint. A summary of programme content is presented in Table 1. The facilitator manual (~100 pages) provides detailed session information, guidance on preparation and delivery, a checklist of facilitator objectives and signposts to additional resources. There is also a companion participant workbook to reinforce material from the programme. Facilitators will be trained at one day orientation workshops and psychological advice and debriefing will be available for facilitators throughout the trial.

**Table 1 T1:** Summary of content of the Fatigue Management Programme

Session	Title	Content	Homework

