#### Data Collection

Trial data will be used to consider the relative effectiveness of the intervention versus comparator, and primary and secondary outcome measures have been described above. Patient level data will be collected within the trial both pre- and post-intervention, and at 4- and 12-month follow-up for those in the fatigue management arm of the trial and equivalent time points post-randomisation for those receiving current local practice. The primary economic analysis of outcomes will be between baseline and 4-month follow-up, although analysis using the shorter time horizon, and other longer term modelled outcomes will also be presented.

Resource use data will be collected over the 4-month follow-up period and will primarily comprise the direct delivery of the group-based cognitive behavioural approach (e.g. staff time, related consumables, and any travel costs for the health professional). Record forms will be used by staff delivering the intervention to identify staff time used, and the main categories of staff time (e.g. delivery of sessions, preparation, setting-up) and semi-structured interviews will be held with each of the Service Providers (centres) to estimate the broader resource use associated with delivery of the intervention.

Further data on NHS and personal social services resource use (e.g. related hospitalisation, Accident and Emergency Department visits, and General Practitioner visits) and information on carer time will be gathered using a simple patient self-completion questionnaire (completed at 4- and 12- month follow-up), and differences between groups will be investigated and reported as part of the economic analysis.

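### Participant-reported NHS, social-service and carer use is asked about for only 3 of the roughly 5.4 to 5.6 months in the primary economic horizon

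*Protocol article*

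**What the plan says.** Under Self-reported resource utilisation: "A resource utilisation questionnaire will be administered at 4- and 12-month follow-up", and the form "includes questions about health and social service contacts in the preceding 3 months". No other recall period is given, and no baseline or 1-month administration is mentioned.

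Under Data Collection in the economic evaluation: "Resource use data will be collected over the 4-month follow-up period", and "The primary economic analysis of outcomes will be between baseline and 4-month follow-up". That section separates two streams. Programme delivery is recorded by staff forms and by interviews with each centre, and is described as the main component. Other NHS and personal social services use and carer time come from the patient questionnaire at 4 and 12 months. Cost Analysis takes all costs other than delivery and related follow-up from that questionnaire. No other source is named.

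The clock is set under Outcome Measures. In the intervention arm baseline is one week before the programme starts, and follow-ups fall "1 month, 4 months and 12 months after the end of the programme". For controls, "outcomes will be sent on the same dates as those randomised to the FMP". Under Intervention: "The intervention consists of six sessions held on a weekly basis".

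**The concern.** The recall period is shorter than the interval over which the costs are needed. The 4-month form looks back 3 months from a date that is itself 4 months after the last session. Everything before month 1 after the programme lies outside its reach, and no earlier form exists to pick it up.

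At stake is the third trial aim, cost-effectiveness. Cost Analysis promises a mean net cost per patient in each arm and an incremental cost with measures of variance. The evaluation also promises a cost per unit change in fatigue and a cost per QALY. QALYs accrue over the whole baseline-to-4-month interval, whereas the participant-reported part of the cost would be observed for little more than half of it. An analysis plan can choose a method of extrapolation, but it cannot recover contacts that no form asked about.

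**Working it through.** The protocol gives no coverage figure to reproduce, so the check is a timeline built from its own schedule.

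**Inputs**
- Baseline: 1 week before programme start (Outcome Measures).
- Programme: six weekly sessions (Intervention). This is 5 weeks from first to last session, or 6 if counted as full weeks; both are carried through.
- Follow-up: 1, 4 and 12 months after programme end, with matched dates for controls (Outcome Measures).
- Recall: 3 months, at the 4- and 12-month forms only (Self-reported resource utilisation).
- Conversion (mine): 1 month = 365.25/12 = 30.44 days.

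**Length of the primary horizon** = pre-programme week + programme + 4 months
- 5-week programme: 7 + 35 + 121.8 = 163.8 days = 5.38 months
- 6-week programme: 7 + 42 + 121.8 = 170.8 days = 5.61 months

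**Part covered by the 4-month form** = months 1 to 4 after the programme = 3 × 30.44 = 91.3 days
- 91.3 / 163.8 = 55.8%
- 91.3 / 170.8 = 53.5%

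**Part never asked about** = horizon − 91.3 days
- 163.8 − 91.3 = 72.4 days (from unrounded values), or 10.3 weeks
- 170.8 − 91.3 = 79.4 days (likewise), or 11.3 weeks

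Even if the clock starts at programme end, 3 of 4 months are covered (75%), so the recall period and the statement about collection disagree on that reading too.

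**What the gap does to the incremental cost.** The missing part equals the length of the gap times the difference between arms in mean cost per unit time during it. Left unscaled, the analysis treats that difference as zero. Scaled pro rata, by 5.38/3 = 1.79 to 5.61/3 = 1.87, it treats the difference as equal to that in months 1 to 4. The protocol does not say which applies.

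**Check of the fix.** A 3-month form at the 1-month mailing reaches back to 2 months (60.9 days) before programme end. Baseline is 42 to 49 days before programme end, so the form reaches past it by 60.9 − 42 = 18.9 days or 60.9 − 49 = 11.9 days. It covers baseline to month 1, and the 4-month form takes over from there.

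**Secondary horizon.** The 12-month form covers months 9 to 12, so months 4 to 9 are not asked about. Coverage from baseline to 12 months is 6/13.38 = 44.8% to 6/13.61 = 44.1%.

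**The case against.** The strongest reply is that the main cost is not missed at all. Programme delivery is named as the primary resource component and is recorded by staff forms and centre interviews. This stands. A reader might infer that the trial fails to cost the programme period; the documents do not support that. The gap concerns only contacts with other services and carer time.

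A reader might also infer that the incremental cost is biased because the arms differ most while the programme is running. The documents do not support this either. Attendance is costed through the staff forms, questionnaires go out on the same dates in both arms, and nothing shows how other service use behaves in those weeks. Incompleteness follows from the text; bias is only a possibility.

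Third, the blank from months 4 to 9 might be taken as a contradiction. It is not: the primary economic horizon ends at 4 months, and longer-term outcomes are announced as modelled.

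It can further be said that the horizon sentence refers to outcomes, that the lead economic endpoint is a cost per change in fatigue between two time points, and that the form may hold items with another recall period. These points soften the mismatch without removing it. The cost per QALY still needs costs and effects over one interval, the text states no other recall period, and the statement about collection speaks of 4 months where the form asks about 3. The planned sensitivity analyses vary estimates of NHS use and unit costs, but the text describes no scaling for unobserved weeks.

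**Conclusion.** The point holds for participant-reported NHS and social-service contacts and carer time. As the text stands, these are observed for about 53% to 56% of the primary economic horizon, and about 10 to 11 weeks are never asked about. The cost per patient in each arm is therefore incomplete for these items. The incremental cost is distorted only if the arms differ in those weeks or if an unsuitable scaling is applied.

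This rests on three assumptions: that the stated 3-month recall applies to all the service-use and carer items, that the forms are completed on schedule, and that the programme lasts 5 to 6 weeks without breaks. The coverage arithmetic is firm under them. The effect on the cost-effectiveness ratio cannot be sized from the protocol. The three clinical primary outcomes are untouched. The change is worth making because the lost information cannot be recovered later.

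**What to change.** Add the unchanged 3-month-recall form to the existing 1-month mailing in both arms. With the 4-month form it covers the whole of baseline to 4 months. Because it also reaches 12 to 19 days before baseline, either name the baseline date as the start of recall on that one form or state how the excess is handled. The cost is one more form for participants who are fatigued, in a trial that has deliberately kept its questionnaires few and short. Lengthening recall on the 4-month form instead would avoid the extra form, but recall would have to reach back about 5.4 to 5.6 months, with more recall error.

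If the schedule cannot change, correct Data Collection to say that these costs are observed for months 1 to 4 after the programme only. State the rule that scales them to the baseline-to-4-month interval, and add a sensitivity analysis on that rule, including different assumptions for the two arms in the unobserved weeks. This costs only wording and some analysis time, but leaves the gap filled by assumption.

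In either case, describe any 12-month cost as modelled rather than observed, since months 4 to 9 are not asked about.

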#### Self-reported fatigue management strategies

To gain deeper insights into the results of the trial, at the 4-month follow-up we will administer a semi-structured questionnaire to participants randomised to the FMP. In the questionnaire (which draws upon an existing questionnaire [66]) they will be asked to describe whether they have tried to make any changes to their lifestyle, behaviour, or thinking, as a result of the intervention; whether these changes have been made successfully or unsuccessfully, and the reasons why. The information they provide will be analysed both quantitatively (for example, number of lifestyle changes, number of successes) and qualitatively (identifying emergent themes in the responses given [67,68]). In this way, we will be able to look closely at "adherence" to the key principles of the intervention, which will help in the interpretation of the trial results.

#### Objective measure of physical activity

The *activ *PAL™ accelerometer classifies an individual's free-living activity into periods spent lying/sitting, standing and walking [69]. This information can be used to estimate daily energy expenditure, and time spent resting. Data will be collected at baseline and at 1- and 4-month follow-up. A postal method of administration was tested during an earlier research phase.

#### Self-reported satisfaction

Participants in the intervention arm will be asked to complete a brief semi-structured evaluation questionnaire at the end of each session of the fatigue management programme. This questionnaire was used in the pilot phases of the research [45].

### Intervention

The group-based fatigue management intervention [45] is based upon a conceptual framework that integrates elements from cognitive behavioural [70], social-cognitive [71], energy effectiveness, self-management [72] and self-efficacy [73] theories.

The intervention focuses on the management of fatigue, the most common symptom of MS, and is likely to be relevant to many people. However, it is expected that it will also provide a framework to help people manage their MS more generally. A cognitive behavioural approach that focuses on one symptom is likely to be clearer and less overwhelming than one encompassing many aspects, can be achieved in a smaller number of sessions, and will be easier to integrate within existing services.

The intervention consists of six sessions held on a weekly basis; the first, 2 hours' duration, and subsequent sessions, 1.75 hours' duration (each with a 15 minute refreshment break halfway through). It is designed to be run by two health professionals with experience of working with people with MS and of group-work (such as occupational therapists, nurses, or physiotherapists). This latter feature enables the intervention to be incorporated into existing health service structures. The intervention will be delivered to groups of 6-12 people.

Participants are encouraged to bring along a "supportive other" to the first session. Since the intervention entails participants making lifestyle changes, the involvement of a "supportive other" could help to encourage and support them in making such changes. Contact between members of the group outside the formal group setting will be encouraged, as an additional source of support.

The intervention is manualised and sessions are delivered via PowerPoint. A summary of programme content is presented in Table 1. The facilitator manual (~100 pages) provides detailed session information, guidance on preparation and delivery, a checklist of facilitator objectives and signposts to additional resources. There is also a companion participant workbook to reinforce material from the programme. Facilitators will be trained at one day orientation workshops and psychological advice and debriefing will be available for facilitators throughout the trial.

**Table 1 T1:** Summary of content of the Fatigue Management Programme

Session	Title	Content	Homework
1	What is MS-related fatigue?	General introduction; expectations; icebreaker (quiz); types of fatigue; contributory factors, conceptual model of fatigue in MS	Activity/fatigue diary

2	Opening an "energy account"	Rest - functions; barriers; relaxation types and techniques; diaphragmatic breathing exercise; sleep hygiene	Rest/activity/sleep planner

3	Budgeting energy & smartening up goals	Types of activity; balancing activity & rest; moderating activity using the toolbox; goal-setting	Goal-setting exercise

4	The stress response; Introducing the cognitive behavioural model	The stress response (fight-or-flight); ways of coping with stress; introducing the cognitive behavioural model	'Unhelpful thoughts related to fatigue' diary

5	Putting unhelpful thoughts on trial	Unhelpful thought patterns related to fatigue; challenging unhelpful thoughts; levels of belief	Thought challenge sheet

6	Recapping & taking the programme forward	Revisiting expectations; group activity to revisit themes of the programme; rationale of 'Keeping on Track' planner	'Keeping on Track' planner

The aim of the intervention is to help people manage their fatigue by:

1. Normalising the experience of fatigue

2. Using their available energy more effectively

3. Developing "helpful thinking styles" about fatigue

#### Missed sessions

If participants do not attend a session they will be sent the materials they missed and, where possible, the session will be held over the telephone. Participants receiving the intervention will continue to have access to services available as part of their usual local care.

### Control group

Participants randomised to this arm of the trial will receive current local practice. Inevitably, there will be minor variations in the exact composition of what is usually provided, both within and between centres; depending on local resources and patient need. We consider this minor variation in current local practice to be a strength of the trial as it will increase the applicability of the findings to a wider range of centres. Individuals who have recently received substantive fatigue management are not eligible for the trial (see exclusion criteria).

